### **4 ELIGIBILITY**

#### **4.1 Inclusion Criteria**

- Adults aged 18 years or over
- Diagnosis of new-onset ISSNHL- sensorineural hearing loss of 30 decibels (dBHL) or greater occurring within a 3-day period and including 3 contiguous pure-tone frequencies (out of 0.5, 1.0, 2.0, 4.0 kilohertz (kHz)) confirmed with a pure tone

---

audiogram occurring within a 3-day period (based on participant reported history)

- Onset of hearing loss within four weeks prior to randomisation
- English spoken as a first or second language

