### 7.3 Technique for intratympanic injection

**Pre-injection testing:** Immediately prior to the second and third intratympanic injections, a pure tone audiogram will be performed and analysed by the treating clinician.

---

**Stopping the intervention early:** If full recovery has been achieved, based on the pre-injection pure tone audiogram (return to within 10 dBHL of the unaffected ear at 0.5, 1.0, 2.0, 4.0kHz (if contralateral ear has no participant reported pre-existing loss)), the participant and clinician may jointly decide to omit further intratympanic injections. This will be recorded in the intervention Case Report Form (CRF) and the participant will continue within the trial.

**Preparing the medication:** Dexamethasone 3.3mg/ml or 3.8mg/ml should be administered depending on local availability and stored according to local policy. It is recommended that 1ml is drawn up in a 1ml syringe using a wide bore needle. A spinal needle (22-25 gauge) should then be attached to the syringe having removed the needle's central trochar. A slight bend at the hilt of the needle facilitates visualisation along the ear canal under a microscope.

**Positioning the participant for injection:** The procedure should be performed using a microscope or endoscope to visualise the tympanic membrane. The participant should lie recumbent on an examination table at an angle of <20 degrees, with the head turned slightly away from the side to be treated.

**Topical anaesthesia of the eardrum:** Any locally adopted method of local anaesthesia can be used, either in cream (most commonly EMLA (lidocaine 2.5% and prilocaine 2.5%)) or liquid form (most commonly co-phenylcaine spray (5% lidocaine + 0.5% phenylephrine) or xylocaine spray (10% lidocaine)). Local anaesthesia is not needed where there is a perforation of the eardrum.

- EMLA cream - The plunger is removed from a 2ml syringe to allow it to be filled with EMLA cream. The plunger is replaced and a blunt needle bent part way down the shaft to allow better visualisation during the application of EMLA cream to the eardrum under an outpatient microscope. It is important that the cream is in contact with the eardrum avoiding air gaps or bubbles. The anaesthetic can take 30 minutes to be effective.

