## **7.7 Intervention modification or cessation**

As specified in section 7.3, complete resolution of hearing may allow intratympanic steroid treatment to be terminated after only one or two treatments. A rare complication of intratympanic injection is further hearing loss. Where this is observed on pure tone audiometry, no further treatments will be given. In the rare event that a study participant chooses to change treatment type or has a significant side effect from oral steroids and is advised to modify or stop the treatment by their treating clinician this will be recorded. On rare occasions, changes to the intervention schedule may be required based on participant request or adverse events. The allocated interventions may be discontinued if a participant requests to cease treatment or cross over to another arm. Adverse events such as allergic reaction, or a change in patient status, such as development of poor blood glucose control may alter the risk-benefit profile for that individual and the treating clinician should discuss this with the patient and alter the provided intervention, if required. Details of treatment

---

adherence, treatment modifications or treatment discontinuation at the Investigator's discretion should be documented in the source data.

Any modification of the interventions, or cross over to another trial arm will also be recorded on the CRFs.

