#### Functional hearing

- **Hearing related to speech: using The Speech, Spatial and Qualities of hearing scale (SSQ).** SSQ is a validated measure, in the form of a short questionnaire, known to provide a good representation of the functional relationship with speech in everyday life and has been used to assess the disability of unilateral hearing loss seen in ISSNHL (19), providing disability scores associated with different aspects of hearing. **(Key secondary outcome)**
- **The absolute improvement in pure tone audiogram average at 6 weeks** following randomisation (calculated at 0.5, 1.0, 2.0, 4.0 kHz). Conducted by an audiologist blinded to the treatment allocation.
- **Actual hearing thresholds** measured by pure tone audiogram average following treatment initiation (calculated at 0.5, 1.0, 2.0, 4.0 kHz).
- **High frequency hearing threshold** measured by the absolute improvement in pure tone audiogram average across 4.0, 6.0 and 8.0 kHz.
- **Recovery of speech perception: using Arthur Boothroyd (AB) word lists scored by phoneme** (19). This speech testing will be carried out by an audiologist blinded to the treatment allocation. This measure is the most widely used in the UK and has a long history of routine use as an assessment tool for single sided hearing loss. Formal training will be provided to the audiologists. Calibration check and test setup will be provided at the training session. Continuing support can be provided throughout the trial where necessary.
- **Extent of hearing recovery: using an established classification of recovery** (complete/partial/none) based on pure tone audiogram and speech perception (1), shown in Table 2.

- 

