#### **Health Economic Assessment**

- Two tools will be used to **assess health economics: the Health Utilities Index 3 (HUI3)**, a participant reported assessment of health-related quality of life suited to hearing loss (24,28), and **ICEpop CAPability measure for Adults (ICECAP-A)**, a participant reported measure of capability for the adult population (29).
- **Resource usage** over the past 12 weeks.

**Table 2:** The relationship between the pure tone audiogram and functional hearing assessments measured in the STARFISH trial, as well as American Academy of Otolaryngology – Head & Neck Surgery hearing recovery criteria (1).

| Degree of hearing recovery | American Academy of Otolaryngology – Head & Neck Surgery criteria / Functional change                                                                                                             | Outcome criteria                                                                                                                             |
|----------------------------|---------------------------------------------------------------------------------------------------------------------------------------------------------------------------------------------------|----------------------------------------------------------------------------------------------------------------------------------------------|
| Unchanged                  | No recovery                                                                                                                                                                                       | 
 
• <10dB change in the pure tone audiogram
 
                                               |
| Partial Recovery Unaidable | Recovery to less-than-serviceable levels indicates an ear unlikely to benefit from traditional amplification.
Can use specialist hearing aid technology but unable to restore spatial hearing. | 
 
• ≥10dB improvement in pure tone audiogram
 
• AB phoneme maximum score <50%
 
     |
| Partial Recovery Aidable   | Recovery to a serviceable level typically indicates that after recovery, the ear would be a candidate for traditional hearing amplification                                                       | 
 
• ≥10dB improvement in pure tone audiogram
 
• AB phoneme maximum score 50% or more
 
 |

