| Full Recovery              | Complete recovery requires return to within 10dBHL of the unaffected ear and                                                                                                                      | 
 
• Return to normal hearing (20dB or lower) or to within 10dB of the contralateral ear
 
      |

Anticipated changes in other outcomes with unchanged hearing:

Unlikely to show a change in HUI3 score

Unlikely to show subjective changes in SSQ and other questionnaires

Anticipated changes in other outcomes partial recovery - unaidable:

Small but negligible improvements might be observed in the SSQ

Other questionnaires might indicate non speech-related improvements

Unlikely to show a change in Health Utilities Index 3 score

Anticipated changes in other outcomes partial recovery - aidable:

SSQ questionnaire will demonstrate functional improvement, which will be supported by other questionnaires

Measurable improvement in the Health Utilities Index 3 score

Anticipated changes in other outcomes with full recovery of hearing:

There will be a large change in the SSQ questionnaire and other questionnaires

Large improvements in the AB phoneme score

Large improvements in the Health Utilities Index 3 score

---

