#### 14.2.2 Secondary outcomes

The secondary outcomes consist of continuous, time to event, binary, ordered categorical with more than two categories and count data types. For all secondary outcomes that are continuous in nature, they will be analysed using the same statistical method as described for primary outcome.

Binary outcomes: For those secondary outcomes that are binary in nature, data will be summarised as number and percentage of participants in each category by intervention arm. An adjusted relative risk and 97.5% confidence interval will be estimated from a log-binomial regression model and the p-value from the associated model will be produced and used to determine statistical significance. We will also present the adjusted risk difference and the corresponding 97.5% confidence interval.

Ordered categorical outcomes with more than two categories: For those secondary outcomes that are categorical in nature with more than two categories, data will be summarised as number and percentage of participants in each category by intervention arm. An adjusted odds ratio and 97.5% confidence interval will be estimated from an ordered logistic regression model and the p-value from the associated model will be produced and used to determine statistical significance.

Time to event outcome: For those secondary outcomes that are time to event data types, these will be compared between intervention arms using survival analysis methods. Kaplan-Meier survival curves will be constructed for visual presentation of time-to-event comparisons. A Cox proportional hazards model will be fitted to obtain an adjusted hazard ratio and 97.5% confidence interval. The p-value from the associated model will be produced and used to determine statistical significance.

Count data: For those secondary outcomes that are count data type, these will be analysed using a Poisson regression model (or negative binomial regression if there is evidence of overdispersion) with an offset for the length of time the participant was in the trial included in the model, to obtain an adjusted incidence rate ratio and 97.5% confidence interval. The p-value from the associated model will be produced and used to determine statistical significance.

---

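### Table 2's recovery classes are neither exhaustive nor mutually exclusive: an ear that worsens by 10 dB or more may have no class, or may be scored Full Recovery

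*Protocol*

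**What the plan says.** Section 8.2.2 lists extent of hearing recovery as a secondary outcome ("complete/partial/none) based on pure tone audiogram and speech perception (1), shown in Table 2"). Table 2 then sets the criteria:

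- Unchanged (second column: no recovery): less than "10dB change in the pure tone audiogram".
- Partial Recovery, unaidable and aidable: "≥10dB improvement in pure tone audiogram", split by whether the maximum AB phoneme score is below 50% or not.
- Full Recovery: "Return to normal hearing (20dB or lower) or to within 10dB of the contralateral ear".

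No row mentions deterioration. Full Recovery carries no minimum improvement, and no order of assignment is given.

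Section 14.2.2 assigns ordered categorical outcomes to one model: "An adjusted odds ratio and 97.5% confidence interval will be estimated from an ordered logistic regression model". Section 14.2 makes the analyses of primary and secondary outcomes intention-to-treat.

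Deterioration is foreseen elsewhere. Section 7.7 states: "A rare complication of intratympanic injection is further hearing loss". Table 5 lists complete sensorineural loss after injection as an expected serious event. Section 7.3 has its own definition of full recovery for its injection rule, and qualifies the comparison with the other ear: "if contralateral ear has no participant reported pre-existing loss". Table 2 has no such qualification.

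**The concern.** An ordered logistic model needs exactly one class per participant. If the written criteria give some ears none and others two, someone must settle the matter later, possibly with outcome data in view.

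The ears without a class are the worst results. Leaving them out conditions the comparison on a post-randomisation outcome that may differ by arm. Pooling them with Unchanged makes deterioration invisible on this scale. Where the other ear is poor, the literal criteria place a deteriorated ear in the best class. Section 1.2.2 says participants suggested this classification so that audiogram data would mean more to them, and a scale that can omit or mislabel deterioration serves that aim poorly.

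**Working it through.** **1. Applying Table 2 literally to example ears** (four-frequency averages in dB; higher is worse)

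| Baseline | Follow-up | Other ear | Change | Classes met |
|---|---|---|---|---|
| 60 | 72 | 10 | 12 worse | none |
| 60 | 72 | 70 | 12 worse | Full only |
| 60 | 60 | 55 | 0 | Unchanged and Full |
| 27.5 | 18.75 | any | 8.75 better | Unchanged and Full |
| 60 | 18 | 10 | 42 better | Full and one partial class |

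The first row is the gap. The second is deterioration scored as the best result. The rest are overlaps.

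**2. Can an eligible ear start that low?** Section 4.1 asks for "sensorineural hearing loss of 30 decibels (dBHL) or greater occurring within a 3-day period and including 3 contiguous pure-tone frequencies" and sets no minimum average. With the fourth frequency at 0 dB the average is (30 + 30 + 30 + 0)/4 = 22.5 dB. With it at 20 dB, the average is 110/4 = 27.5 dB. A fall to 20, 20, 20 and 15 dB gives 75/4 = 18.75 dB. The gain of 8.75 dB is under 10, yet hearing is normal.

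On the wording, a worsened ear could also count as Full by still being at 20 dB or lower. From an eligible 22.5 dB, a 10 dB loss leads to 32.5 dB, so in practice the route is the comparison with the other ear.

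**3. How many ears worsen by 10 dB or more?** Table 2 states no frequency. The only planning figures are in section 14.1: control gain 25, SD 25, difference 10, two-sided alpha 0.025, power 90%. They reproduce the sample size: 2 × (2.241 + 1.282)² × (25/10)² = 155.1, so 156 per arm by the normal formula. The t-test version gives 156.4, rounded up to 157. Then 157/0.9 = 174.4, so 175 per arm and 525 in total, as stated.

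Assuming normal gains, which the protocol does not state:

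- Mean 25, SD 25: Φ((−10 − 25)/25) = Φ(−1.4) = 0.081, and 157 × 0.081 is about 13 ears.
- Mean 35, SD 25: Φ(−1.8) = 0.036, about 6 of 157.
- Means of 15 to 35 with SDs of 20 to 30 (assumed ranges): 1.2% to 20.2%.

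**4. Does the handling matter?** From the same normal model:

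| Mean gain | Worse by ≥10 | Within 10 | Improved by ≥10 |
|---|---|---|---|
| 25 | 0.081 | 0.193 | 0.726 |
| 35 | 0.036 | 0.123 | 0.841 |

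Odds ratio for improved against not improved, with worsened ears pooled with Unchanged: (0.841/0.159)/(0.726/0.274) = 2.00. With worsened ears dropped: (0.841/0.123)/(0.726/0.193), which is 1.83 on unrounded values. Here dropping understates the benefit.

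The direction can differ. Take two arms of 157 with 31, 31 and 48 ears in the two partial classes and Full. One arm has 8 worse and 39 unchanged, the other 24 worse and 23 unchanged. These counts are illustrative and have no source in the protocol. The ordered logistic odds ratio for the second arm is:

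- worsened ears dropped: 1.33 (97.5% CI 0.82 to 2.16);
- pooled with Unchanged: 1.00;
- given their own lowest class: 0.91 (0.58 to 1.43).

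**The case against.** The strongest reply is that the protocol never says worsened ears are excluded. Section 14.2 wants all participants analysed as randomised, section 8.2.2 calls the lowest level none, and Table 2 labels that row no recovery. An ear that got worse has not recovered, so a sensible analyst would put it there. This stands in part: on that reading nothing is reversed, and deterioration is only hidden. But the row's own criterion, a change of less than 10 dB, excludes such an ear.

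Second, deterioration is captured elsewhere: as a negative value in the continuous primary outcome, in the actual thresholds, and as an adverse event. This stands, and it limits the consequences. The adverse event item concerns sudden deterioration and sits on the 6-week form. The 12-week form records only perforation.

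Third, the overlap looks like an edge case. Return to normal hearing suggests that the ear started outside it, and taking the best class met is a natural habit. For the 27.5 to 18.75 dB ear this is fair. It does not help an unchanged 60 dB ear beside a 55 dB ear, which that habit would call Full.

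Fourth, a SAP may set the derivation. It may, but the protocol already fixes these criteria, and they need correcting where they stand.

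A reader might also see a contradiction between the three levels named in section 8.2.2 and the four in Table 2. There is none: Table 2 splits partial recovery in two.

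**Conclusion.** Applied as written, Table 2 gives some ears no class, some two, and some deteriorated ears the best class. That follows from the criteria alone and needs no assumption.

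The size is uncertain. The 8.1% rests on assumed normality and on planning figures chosen for sample size. It is probably too high, since section 7.7 calls further loss after injection rare.

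A reader might infer that the plan turns harm from injection into apparent benefit. The documents do not support that. It requires worsened ears to be excluded, which no section says, and an excess of worsening after injection for which no rate is given. In the illustration above the interval includes 1, and on the planning figures dropping worsened ears shrinks a true benefit. What the documents do support is that the result depends on an unstated choice: deterioration is hidden if pooled, and the comparison is biased if such ears are excluded.

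The effect is confined to one secondary outcome, which is not the key one (SSQ). The primary outcome and the sample size are unaffected.

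**What to change.** In Table 2:

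- Add a lowest class Worse: deterioration of 10 dB or more.
- Define Unchanged as a change of less than 10 dB in either direction.
- State one order of assignment: Worse first; then Full, only if its criterion was not already met at baseline; then Partial, by AB score; then Unchanged.

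Reconcile Table 2's contralateral-ear criterion with the condition on pre-existing loss in section 7.3. This concerns the outcome definition only, and no change to the injection rule is proposed. Use the same levels in section 8.2.2 and in the ordered logistic model, and report the Worse share by arm.

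Under this order an ear that already met the Full criterion at baseline cannot be classed Full, so the number of such ears should be reported by arm.

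The cost is a few words in Table 2 and section 8.2.2. Audiograms of both ears and AB scores are already planned, so no new data and no extra participants are needed.

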#### 10.4.2 Serious Adverse Events requiring non-expedited reporting to BCTU

Where the safety profile is well established, the causal relationship between the intervention (or the participant’s underlying condition) and the SAE, may be known. That is, such events are protocol-defined as “expected”.

Such events should still be recorded in the participant’s medical notes and reported to BCTU on the SAE form (as per section 10.5) but it does not require expedited reporting (immediately on the site becoming aware of the event) since the assessment of expectedness for the specified events has been pre-defined. These should be reported in line with the expected timeframes for other CRFs, i.e. within 4-weeks of becoming aware of the event. These events are detailed in Table 5 below.

**Table 5:** Expected SAEs in STARFISH

| Expected events related to oral steroids                  | Expected events related to intratympanic injection      | Expected events related to both oral steroids and intratympanic injection |
|-----------------------------------------------------------|---------------------------------------------------------|---------------------------------------------------------------------------|
| Blood glucose derangement requiring hospitalisation       | Complete sensorineural hearing loss following injection | Allergic reaction requiring hospital treatment                            |
| Psychotic or affective disorder requiring hospitalisation |                                                         |                                                                           |

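### Table 2 does not place every ear in exactly one ordered recovery level: some worsened ears fit no row, and Full Recovery overlaps all the others

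*Protocol*

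**What the plan says.** The extent-of-recovery outcome in Protocol section 8.2.2 is described as "complete/partial/none) based on pure tone audiogram and speech perception (1), shown in Table 2". Table 2 then prints criteria for four levels:

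- **Unchanged** (also labelled as no recovery): less than a "10dB change in the pure tone audiogram".
- **Partial Recovery Unaidable**: "≥10dB improvement in pure tone audiogram", with an AB phoneme maximum below 50%.
- **Partial Recovery Aidable**: the same improvement, with "AB phoneme maximum score 50% or more".
- **Full Recovery**: "Return to normal hearing (20dB or lower) or to within 10dB of the contralateral ear".

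No precedence among the rows is stated. Four other places bear on how the criteria work:

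- Section 4.1 requires "sensorineural hearing loss of 30 decibels (dBHL) or greater occurring within a 3-day period and including 3 contiguous pure-tone frequencies", out of four tested, so the four-frequency average at entry can be below 30 dB.
- Section 4.2 excludes bilateral ISSNHL but not a pre-existing loss in the other ear.
- Section 7.3 also defines full recovery against the other ear, for the decision on further injections. It adds a condition that Table 2 lacks: "if contralateral ear has no participant reported pre-existing loss".
- Section 14.2.2 analyses ordered categorical outcomes with more than two levels by ordered logistic regression.

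**The concern.** An ordered logistic model needs each participant in exactly one of a set of ordered levels. The Table 2 criteria do not deliver that.

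First, the table says change in one row and improvement in the next two. Read as printed, an ear that worsens by 10 dB or more, and does not meet the Full criterion, has no row. The protocol itself expects some worsening. Section 7.7 names further hearing loss as a rare complication of injection, section 10.3 lists sudden deterioration as a targeted adverse event, and Table 5 in section 10.4.2 lists "Complete sensorineural hearing loss following injection" among expected serious events.

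Second, Full Recovery depends only on the final level, so it can hold for an ear that has hardly changed, or has got worse, when the other ear is poor.

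Two analysts could therefore assign the same ear to different levels, and the choice could be made after outcomes are known.

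**Working it through.** The plan states no figure that depends on Table 2, so there is none to reproduce. The check applies the printed criteria to possible ears. Let B be the baseline average, F the follow-up average, C the contralateral average (all in dB over the four frequencies) and AB the maximum phoneme score. Using averages is an assumption, because Table 2 does not say whether its limits apply to the average or to each frequency.

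- Unchanged: |B − F| < 10
- Partial Unaidable: B − F ≥ 10 and AB < 50%
- Partial Aidable: B − F ≥ 10 and AB ≥ 50%
- Full: F ≤ 20, or F − C ≤ 10

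| Case | B | F | C | AB | Rows met |
|---|---|---|---|---|---|
| 1 | 60 | 75 | 10 | 20% | none |
| 2 | 23.75 | 20 | 10 | 90% | Unchanged and Full |
| 3 | 60 | 55 | 50 | 70% | Unchanged and Full |
| 4 | 60 | 15 | 10 | 95% | Partial Aidable and Full |
| 5 | 60 | 75 | 70 | 20% | Full |

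**Case 1.** The ear worsens by 15 dB. It is not Unchanged (15 ≥ 10), not Partial (no improvement) and not Full (75 > 20; 75 − 10 = 65 > 10).

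**Case 2.** Thresholds of 30, 30, 30 and 5 dB meet the entry level, and their average is (30 + 30 + 30 + 5)/4 = 23.75. A fall to 20 is a change of 3.75 dB. Reading the limit per frequency does not help: 20, 20, 20 and 5 dB average 16.25, a change of 7.5 dB, still under 10.

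**Case 3.** The change is 5 dB, and 55 − 50 = 5 is within 10 of the other ear.

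**Case 4.** Any ear that reaches Full with at least 10 dB of improvement also meets one of the Partial rows. With AB below 50%, this ear would meet Partial Unaidable and Full.

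**Case 5.** The ear is 15 dB worse, but 75 − 70 = 5, so it meets Full and nothing else.

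**When Unchanged and Full can both hold.** By the normal-hearing route, F ≤ 20 and B − F < 10 require B < 30. By the contralateral route, F ≤ C + 10 and B − F < 10 require B < C + 20. Eligibility permits both.

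**Alternative reading.** If change in the Unchanged row means improvement (B − F < 10), case 1 becomes Unchanged and the gap closes. Cases 2, 3 and 4 still meet two rows each, and case 5 now meets Unchanged and Full.

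**The case against.** The best defence is that the intended meaning is easy to guess. The table grades recovery, its bottom row is also labelled as no recovery, and section 8.2.2 calls the lowest level none, so a worsened ear belongs there. A full recovery is plainly not a partial one, so the highest row met presumably applies. The word return suggests some improvement. Derivation order is ordinary SAP content.

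Much of this stands as a guide to intent. But the criteria are fixed in the protocol, and what they say differs from that intent. A highest-row-first rule settles case 4, but it makes cases 3 and 5 Full Recovery, which nobody would intend. Return rules out an ear with no change, but not 60 to 55 dB.

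A reader might infer several stronger points that the documents do not support:

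- **The gap flatters the injection arms.** This follows only if worsened ears are dropped and are commoner in those arms. Nothing says they are dropped, section 14.2 commits to intention to treat, and section 10.3 lists deterioration for all arms. As an illustration on assumed rates, let 40% be in the worst level in both arms, with 4% worsening by 10 dB or more on injection and 1% on oral. Dropping them gives (40 − 4)/96 = 37.5% against (40 − 1)/99 = 39.4%, with odds of 0.600 and 0.650 and a ratio of 1.08. With equal rates, or with worsened ears placed in the bottom level, the ratio is 1.00. The standard error of a log odds ratio at 157 per arm is about √(2/(157 × 0.4 × 0.6)) = 0.23, so even the illustrated shift (log 1.08 = 0.08) is about a third of it.
- **Three levels in the text contradict four rows in the table.** They do not: the two Partial rows nest within partial.
- **The economic evaluation inherits the fault.** Section 15 mentions increments of hearing improvement but never ties them to Table 2.
- **The Full row is incomplete.** Its descriptive cell breaks off mid-sentence, which may be an effect of reading the PDF and is not counted here.

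**Conclusion.** The point holds as a defect in stated criteria. As printed, Table 2 is neither exhaustive nor mutually exclusive. The gap for worsened ears rests on reading change in its plain, two-directional sense; the overlaps hold on either reading. The missing condition on contralateral loss also leaves Table 2 and section 7.3 with different definitions of full recovery, and these need reconciling.

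The size is unknown. The documents do not say how many participants enter with an average below 30 dB, have a poor other ear, or worsen by 10 dB or more. With an expected control-group gain of 25 dB (section 14.1), ears near the 20 dB route's limit may be few, but the SD is also 25 dB. No direction of bias is established.

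The reach is limited. This is one secondary outcome, and SSQ, not this one, is the key secondary. The primary outcome is continuous and registers worsening directly. The sample size and the capture of adverse events do not depend on Table 2.

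**What to change.** Change the wording of Table 2 and section 8.2.2 before outcome data are seen:

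1. Redefine the bottom level as less than 10 dB of improvement, including any worsening, or add a separate level for ears that worsen by 10 dB or more.
2. State that levels are assigned in a fixed order, starting with Full, so that each ear receives one level.
3. State how an ear that meets the Full criterion with less than 10 dB of improvement is classed. An unchanged or worsened ear should not count as Full merely because the other ear is poor. Equally, an ear that truly returns to normal, or to its pre-existing symmetric level, should not be denied Full.
4. Reconcile Table 2 with section 7.3 on contralateral loss.
5. Name the four (or five) levels in section 8.2.2 and use the same levels in the ordered logistic model.

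On item 3, two simple repairs would introduce new errors. Requiring 10 dB of improvement for every Full ear would class 28 to 20 dB as no recovery. Disallowing the contralateral criterion whenever the other ear has an old loss would bar a participant with symmetric 35 dB hearing from Full even after regaining it completely. One workable wording asks for some improvement on the normal-hearing route and at least 10 dB on the contralateral route. It makes case 2 Full and cases 3 and 5 no recovery, and it keeps a 65 to 35 dB ear opposite a 35 dB ear as Full. It leaves the team to decide about an ear that reaches the other ear's level with a smaller gain.

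The cost is a wording amendment and matching SAP text. Every level derives from audiograms and AB scores already scheduled.
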